### Statistical analysis

2.8

The data obtained from the subjects of this study will be analyzed in the form of a full analysis set (FAS) analysis group and a per protocol (PP) analysis group. The FAS analysis group refers to analyzing a set of subjects that minimizes those who are excluded, except for a legitimate reason, from the analysis among the randomly assigned subjects. The PP analysis group refers to analyzing a set of subjects who have participated in more than 75% of the interventions (3 or more interventions) specified in this study's protocol and have not violated this study's protocol, and for whom the assessment variables have been measured completely. Both the FAS analysis group and the PP analysis group will be used for the effectiveness analysis while the main analysis group will be the FAS analysis group and the auxiliary confirmation will be performed by using the PP analysis group.

All statistical analyses will be conducted using the 2-tailed test in principle, and the significance level will be set at 5%. Analyses will use the statistical program SAS Version 9.4 (SAS Institute, Inc, Cary, NC). When missing values are encountered, they will be processed using multiple imputations.

The descriptive statistics of the subjects’ demographic characteristics and clinical baseline variables, such as gender, age, history, and drug dosage, will be presented for each treatment group. If the comparisons between the 2 groups involve continuous data, the mean and the standard deviation will be presented, and analyses will be performed using the independent *t* test or the Wilcoxon rank sum test. As needed, the 95% confidence interval will be provided. If the comparisons between the 2 groups involve categorical data, the frequency and the percentile will be presented, and analyses will be performed using the chi-square test or the Fisher exact test.

The primary outcome variable is the mean changes in the score on the VAS at 4W compared with the baseline and will be analyzed using an analysis of covariance with the covariates being the VAS score at baseline and the fixed factor that in each treatment group. Secondary outcome variables will be analyzed in the same manner as the primary outcome variable. If the outcome variables are categorical data, they will be analyzed using the chi-square test or the Fisher exact test. If necessary, a paired *t* test or Wilcoxon signed-rank test will be used for the primary and the secondary outcome variables to analyze differences in measured values before and after treatment in each group, and a repeated measures analysis of variance will be performed to test the difference in the trend at each visit. The Dunnett procedure will be used for multiple comparisons.

If necessary, subgroup analyses of outcome variables, such as demographic variables measured at baseline (e.g., gender, age, duration of illness, treatment expectancy, etc.), whether or not rescue medicines were taken, the amounts of rescue medications taken, the hospital at which the subject was treated, etc., may be conducted. The safety assessments will primarily be performed by analyzing the frequency of adverse events and SAEs that the researchers suspect to be associated with treatment. The collected safety data will be appropriately summarized. All adverse events that occur will be listed with a detailed description. All SAEs will be recorded descriptively. Adverse events will be collected through patient symptom reports and researcher observations. The frequency of each adverse event associated or not associated with intervention will be recorded and analyzed using descriptive statistics. No interim analysis will be performed.

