### Outcome measures

2.6

Assessments will be conducted at baseline and at 2 weeks (2W), 4 weeks (4W), and 6 weeks (6W) after randomization. The assessments at baseline and 2W during the intervention period will be performed before the assigned intervention for that visit. The schedule for the assessments of the results is shown in Table 2.

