**Table 2 T2:**
[figure not shown]
Schedule for the treatment and the outcome measurements.

The primary outcome is the mean change in the VAS score for back and/or leg pain at 4W compared with baseline. The baseline VAS score will be measured immediately before the first intervention. The subject will indicate the degree of back and/or leg pain on a straight line of 100 mm. On that line, the left endpoint, 0, is no pain, and the right endpoint, 100, is the maximum pain imaginable.^[18]^

The secondary outcomes include back and/or leg pain at other time points, the clinical relevance^[19–22]^, dysfunction of the lumbar spine, range of motion of the lumbar spine, quality of life, and global assessment.

The clinical relevance will be assessed by comparing the percentage of subjects who indicate an improvement of more than 15 mm on the VAS, which corresponds to the Minimal Clinically Important Difference (MCID), of more than 30%, and of more than 50% between the 2 groups. In 2008, a consensus statement was issued that recommended MCID values for chronic pain assessment tools (pain, dysfunction, psychological factors, quality of life, etc.). According to a study that investigated the clinical relevance of the VAS for chronic back pain, the MCID was found to be greater than 15 mm based on the VAS (0–100 mm). Thus, in this study, we compare the proportions of subjects who have a decrease in the VAS score of 15 mm in each of the 2 groups. According to the above recommendation, in assessments using the VAS or the NRS, reductions of more than 30% and 50% in the MCID in chronic pain research suggest moderate clinically important changes and substantial improvements, respectively. Therefore, the main assessment tool of this study will be the VAS, so we will use it according to the criteria of the above recommendations.

The dysfunction of the lumbar spine will be assessed by using the mean changes in the scores on the Korean version of the Roland Morris Disability Questionnaire (RMDQ)^[23–26]^ at 2W, 4W, and 6W compared with baseline. The RMDQ was designed to measure the physical dysfunction of patients with back pain. Twenty-four questionnaire items will be simply answered “Yes (1) / No” (0), and the questionnaire will be scored from 0 to 24. A higher score indicates a greater degree of dysfunction. This survey has 2 advantages: the respondents can quickly complete the survey and the survey is easy to apply.

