The range of motion of the lumbar spine will be assessed by using the mean changes in the measured values on the Modified-Modified Schober Test (MMST)^[27,28]^ at 2W, 4W, and 6W compared with baseline. The MMST is a physical examination that assesses lumbar vertebrae mobility. With the subject standing straight, the end points 10 cm above and 5 cm below a straight line based on the point where the mid-line of the vertebrae and the connection-line of both Posterior Superior Iliac Spines meet will be marked. Then, the researching physician will let the subject bend his or her lower back forward to the maximum extent while still feeling no pain and will then measure the amount of change in the distance between the 2 points.

The quality of life will be assessed by using the mean changes in the scores on the Korean version of the EuroQol Five Dimensions questionnaire (EQ-5D)^[29,30]^ at 2W, 4W, and 6W compared with baseline. The EQ-5D is the most widely used tool for measuring quality of life. Hence, only the EQ-5D Index will be used in this study.

The global assessment will be done by using the Patient Global Impression of Change (PGIC)^[31]^ at 4W. The PGIC is a method for assessing the alleviation of the symptoms that the subjects have felt themselves before and after treatment. The subjects are able to choose from 7 categories of responses to how much the back and/or leg pain has been reduced compared with before their participation in this study.

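### The per-protocol set requires complete assessment variables without limiting this to the outcome or visit analysed, so the supportive 4-week VAS analysis is partly selected on data collected after week 4

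*Protocol article*

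**What the plan says.** Section 2.8 of the protocol article sets three joint conditions for the PP set. The subject must have "participated in more than 75% of the interventions (3 or more interventions) specified in this study's protocol", must not have violated the protocol, and must be one "for whom the assessment variables have been measured completely". I take the parenthesis, 3 or more of the 4 sessions, as the working attendance rule. Neither the violation condition nor the completeness condition is tied to a particular outcome, visit or cut-off date.

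The same section fixes the role of the set: "the main analysis group will be the FAS analysis group and the auxiliary confirmation will be performed by using the PP analysis group". Missing values are to be handled by multiple imputation.

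Section 2.6 gives the timing. "Assessments will be conducted at baseline and at 2 weeks (2W), 4 weeks (4W), and 6 weeks (6W) after randomization". "The primary outcome is the mean change in the VAS score for back and/or leg pain at 4W compared with baseline". Secondary scales run beyond that point. For example, quality of life is measured with the "EuroQol Five Dimensions questionnaire (EQ-5D)^[29,30]^ at 2W, 4W, and 6W compared with baseline", and RMDQ and MMST follow the same schedule.

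**The concern.** The PP analysis of the primary outcome needs a baseline VAS, a 4-week VAS and enough treatment. The definition asks for more. A subject who received all four sessions and gave a valid 4-week VAS can be removed from that analysis because the 6-week visit was missed, or because one RMDQ, MMST, EQ-5D or PGIC value is absent. Neither event says anything about adherence to the two-week treatment course or about the 4-week measurement.

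The issue is one of selection more than of numbers. Whether a subject returns at week 6 may depend on how much pain was left at week 4, so the supportive set is partly chosen on a possible consequence of the outcome. Section 2.4 says that patients and treating clinicians cannot be blinded, and section 3 says that expectation effects cannot be excluded. Section 2.5.2 offers acupotomy after the trial to the manual acupuncture arm only. Retention after week 4 could therefore differ between arms. That it would differ is my inference; the article does not state it.

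The PP set also has complete outcomes by construction, so multiple imputation of outcomes has nothing to do there. A disagreement between the full analysis set (FAS) and the PP set would mix adherence, violations, late completeness and missing-data handling.

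**Working it through.** **Inputs.** From section 2.3: difference 15, SD 24.71, 5% significance, 90% power, 1:1 allocation, 20% dropout, 73 per group. From section 2.8: two-sided tests. The share f of dropout that falls after the 4-week VAS is not given, so it is varied.

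**The plan's own figure.** n = 2 × [24.71 × (1.960 + 1.282) / 15]² = 57.03, rounded up to 58 per group. 58 / 0.80 = 72.5, rounded up to 73 per group, 146 in total. This reproduces the plan, and the sample size is not at issue.

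**Subjects discarded through dropout alone.**
- Kept under the rule as written: 73 × 0.80 = 58.4 per arm, whatever f is.
- Kept if only baseline and 4-week VAS are required: 73 × [1 − 0.20 × (1 − f)].
- SE ratio: square root of (second number / first number).

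| Share f after 4W | 4W VAS available, per arm | Complete to 6W, per arm | Discarded, per arm | SE ratio | Power, endpoint rule vs as written |
|---|---|---|---|---|---|
| 0% | 58.4 | 58.4 | 0 | 1.00 | 0.907 vs 0.907 |
| 25% | 62.0 | 58.4 | 3.6 | 1.03 | 0.922 vs 0.907 |
| 50% | 65.7 | 58.4 | 7.3 | 1.06 | 0.936 vs 0.907 |
| 75% | 69.3 | 58.4 | 10.9 | 1.09 | 0.947 vs 0.907 |

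Power is by normal approximation at difference 15 and SD 24.71.

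**Even spread.** If dropout is spread equally over the intervals ending at 2, 4 and 6 weeks:
- Dropouts per arm: 73 × 0.20 = 14.6, one third of which is 4.9.
- With a 4-week VAS: 73 − 9.7 = 63.3. Complete to 6 weeks: 58.4.
- SE ratio: √(63.3 / 58.4) = 1.04.

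**Missing items among 6-week completers.** The documents give no rate. If an assumed 5%, 10%, 15% or 20% of the 58.4 lack at least one required value, the PP set falls to 55.5, 52.6, 49.6 or 46.7 per arm, with power 0.892, 0.875, 0.856 or 0.835.

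All counts ignore PP exclusions for attendance or violations.

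**The case against.** **The wording may be meant more narrowly.** The text does not say that every variable at every visit is required, and section 2.8 analyses outcomes one at a time. Completeness could mean completeness of the variable under analysis, and the full protocol may say so. This stands as a caution. But the phrase is plural and unrestricted, the PP set is defined once, and nothing in the article narrows it. The plain reading is the broad one.

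**The primary inference is safe.** The FAS is the main set, missing values are imputed, and no success criterion rests on the PP set. This stands in full. A reader might infer that the primary result itself is compromised, and the documents do not support that.

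**On dropout alone the strict set reaches the planned size.** It keeps 58.4 per arm against 58 required. This also stands, so the numerical loss is a minor part of the point.

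**One common set has a merit.** All outcomes are then confirmed in the same subjects. That is true, but the price is selecting the 4-week analysis on later data.

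Two stronger readings are tempting:

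- *Seeking other care in week 5 removes a subject from the 4-week PP analysis.* Section 2.5.3 tells subjects not to take other treatment, but it drops a subject who does only if the principal investigator judges that the study outcomes could be significantly affected. The article does not say whether such a lapse after week 4 counts as a PP violation, so this is possible but not established.
- *The PP set shrinks to about 49 per arm against 62, with a 12% larger SE.* This needs 17 measurements per subject (VAS, RMDQ, MMST and EQ-5D at four times, PGIC once), each independently missing in 1%. Then 1 − 0.99¹⁷ = 15.7%, 58.4 × 0.843 = 49.2, 63.3 × 0.99² = 62.0 and √(62.0 / 49.2) = 1.12. The 1% is not in the documents. Scales are collected together at visits, so gaps would tend to cluster, which lowers the number of subjects affected.

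**Conclusion.** The point holds as a weakness in the definition of a supportive analysis. On its plain reading, the PP rule removes treated subjects with a valid 4-week VAS because of data missing after the primary endpoint, or because of unrelated scales. The main cost is to interpretation, since the set offered as confirmation is partly selected on later completeness in a trial with unblinded patients.

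The precision loss is modest. It runs from none, if all dropout precedes week 4, to about 11 subjects per arm if 75% of dropout follows it. With dropout even over the three intervals it is about 4.9 per arm and a 4% larger SE. Item missingness would add to this by an amount the documents do not allow anyone to fix. These figures rest on the stated 20% dropout, an assumed timing, and no other PP exclusions. The change is worth making because it is cheap.

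**What to change.** Define PP membership per outcome in section 2.8 and carry the definition into the analysis plan before the data are analysed:

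- **Primary outcome.** Require the attendance criterion, no protocol violation up to the 4-week assessment, and observed baseline and 4-week VAS. Missing 6-week data or missing secondary scales do not exclude a subject.
- **Each secondary outcome.** Apply the matching rule: no violation up to the visit concerned, and that variable observed at that visit and, where a change is analysed, at baseline.

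The cost is one sentence, with no extra data or patients. PP sets will differ in size across outcomes, so the number analysed should be reported with each result. The repaired set still conditions on events after randomisation (attendance, violations and an observed 4-week VAS), so a difference between FAS and PP still cannot be read as a pure effect of adherence. The change removes only the selection on later or unrelated data.

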### Study design

2.2

This study will be performed as a multicenter, 2-arm parallel design, stratified block (male vs female) randomized, assessor-blinded, controlled, clinical trial. The flowchart for this trial is shown in Fig. 1. This study will recruit 73 applicants per group, for a total of 146 applicants, who meet the inclusion and the exclusion criteria (Table 1).^[13]^ A total of 146 patients with LDH will be recruited from outpatients at the Daejeon University Dunsan Korean Medicine Hospital (DUDKMH) and the Daejeon University Cheonan Korean Medicine Hospital through advertisements posted on bulletin boards at subway stations, apartments, and hospitals and on subway cars, hospitals’ homepages, newspapers, etc. Recruitment commenced in March 2018, and the trial is expected to end in February 2019.

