### Sample size calculation

2.3

Based on the results of a pilot study and clinical significance, we assume that the mean difference (δ) between the changes in the VAS before and after treatment in each group is 15 and the standard deviation (σ) is 24.71. When a significance level of 5%, a power of 90%, and an assignment ratio of the groups of 1:1 are applied, the number of subjects in each group (n) is given by^[14]^ 

Also, for an expected dropout rate of 20%, according to 

at least 73 subjects per group are required, for a total of 146 subjects.

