### Randomization and blinding

2.4

The randomization will be performed by using a random number table that is generated by using the statistical program SAS Version 9.4 (SAS Institute Inc, Cary, NC) and is kept secret by the statisticians who are independent of this study. Stratified block randomization, which uses gender as a stratification factor, will be performed so that the sex ratio, which is the factor affecting the treatment, will be balanced in the 2 groups.^[15]^

This study is designed so that assessors, data collectors, and statisticians are blinded to the group assignment of the participants. Researchers who do not perform the intervention and randomization will assess the subjects. The assessment items and the contents for the purpose of completing the case report form (CRF) will be simply discussed with minimal dialogue, but will be closely evaluated. Furthermore, the study will be conducted in such a manner that the researchers will not know what intervention the subject is receiving. However, in this study, the 2 interventions are so different that blinding the clinicians and the subjects will be impossible. Thus, the clinicians of acupotomy and those of manual acupuncture will be separated from each other, and each clinician will perform only 1 kind of intervention; this should prevent biases due to intentional intervention by the clinicians. Moreover, the intervention clinicians will not participate in any assessment.

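### The primary ANCOVA omits sex, the only factor by which randomisation is stratified; adding it costs one degree of freedom and makes the analysis match the design.

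*Protocol article*

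**What the plan says.** The protocol article, section 2.2 (Study design), describes a "multicenter, 2-arm parallel design, stratified block (male vs female) randomized, assessor-blinded, controlled, clinical trial", recruiting at two hospitals. Section 2.4 (Randomization and blinding) sets out the strata and the reason for them, in a scheme "which uses gender as a stratification factor, will be performed so that the sex ratio, which is the factor affecting the treatment". No other stratification factor is named.

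Section 2.8 (Statistical analysis) then fixes the primary model. The change in VAS at 4 weeks is to be "analyzed using an analysis of covariance with the covariates being the VAS score at baseline and the fixed factor that in each treatment group". The secondary outcomes follow the same approach, except that categorical ones get a chi-square or Fisher exact test. Sex and hospital appear in section 2.8 only as possible subgroup variables, to be used if necessary; for hospital the wording is "the hospital at which the subject was treated, etc., may be conducted".

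**The concern.** The design and the analysis rest on different premises. Sex is important enough to restrict the randomisation but does not enter the model. When a prognostic factor is balanced by design, the treatment estimate varies less from trial to trial than it would under simple randomisation. A model without that factor cannot see this. It counts the variation due to sex as residual error and reports a standard error that is too large. Confidence intervals are then somewhat wide, the test rejects a true null hypothesis less often than 5%, and some of the benefit of stratifying is given up.

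This is not a detail that a condensed article leaves to a fuller plan. Section 2.8 lists the covariate and the factor, and the list omits the stratification factor.

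**Working it through.** **Inputs from section 2.3 (Sample size calculation).** Difference in VAS change 15 mm, SD 24.71, alpha 5%, power 90%, allocation 1:1, dropout 20%. Section 2.8 makes tests two-sided.

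**The plan's own figure.** n per arm = 2 × (24.71)² × (1.960 + 1.282)² / 15² = 57.03, rounded up to 58. Allowing for dropout, 58 / (1 − 0.20) = 72.5, rounded up to 73. This reproduces the stated 73 per group and 146 in total.

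**Assumptions.** Let r² be the share of residual variance, after baseline VAS, that sex explains. The article does not give it, so 0%, 2%, 5% and 10% are shown. There are 58 completers per arm, 24.71 is used as the residual SD of the model without sex, and a normal approximation is used. The standard-error and alpha results do not depend on the SD; the power results do.

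**Formulas.**
- Standard error reported without sex: 24.71 × √(2/58) = 4.59 mm, so 15 / 4.59 = 3.269 standard errors.
- Actual standard error under sex-stratified randomisation: 4.59 × √(1 − r²).
- Overstatement of the reported standard error: 1/√(1 − r²) − 1.
- Actual alpha without sex: 2 × [1 − Φ(1.96/√(1 − r²))].
- Power without sex: Φ[(3.269 − 1.96)/√(1 − r²)].
- Power with sex: Φ[3.269/√(1 − r²) − 1.96].

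| r² for sex | Reported SE too large by | Actual alpha without sex | Power without sex | Power with sex | Gain (points) |
|---|---|---|---|---|---|
| 0% | 0% | 5.0% | 90.5% | 90.5% | 0 |
| 2% | 1.0% | 4.8% | 90.7% | 91.0% | 0.3 |
| 5% | 2.6% | 4.4% | 91.0% | 91.8% | 0.8 |
| 10% | 5.4% | 3.9% | 91.6% | 93.1% | 1.5 |

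By these formulas, alpha with sex in the model is 5% in every row. Power without sex also rises with r², because stratification lowers the true variance whatever model is fitted. The gain is therefore the difference within each row, not the distance from 90%.

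**Simulation check.** 116 completers, sex-stratified blocks of 4, equal sex split (both assumed), 5,000 runs per scenario.
- r² = 10%: the mean reported standard error was about 4.60 without sex and 4.37 with sex, against an actual SD of the estimate of about 4.35 to 4.38. Type I error was 0.040 without sex and 0.051 with it.
- r² = 2% and 5%: effects on type I error are close to the Monte Carlo error of about 0.003, √(0.05 × 0.95/5000). The simulated rates were 0.045 against 0.048 and 0.050 against 0.055, without and with sex. The direction is as expected, but these runs do not fix the size.
- r² = 0: the mean reported standard error was 4.59 with or without sex, so the extra term costs practically nothing.

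**Hospital.** With hospital explaining 5% of residual variance, an equal split assumed, and no stratification by it, the mean reported standard error without hospital was about 4.60. The actual SD of the estimate was 4.70 in the null run and 4.56 in the 15 mm run, and type I error was 0.056. That agrees with a valid standard error to within simulation error. Adding hospital lowered the standard error to about 4.50 and raised power from 90.3% to 91.1%, roughly 1 point.

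**The case against.** The strongest objection is that the harm is conditional, conservative and small. The article does not say how well sex predicts VAS change. Its remark that sex affects the treatment has no size attached and does not separate prognosis from response to treatment. If sex adds nothing after baseline VAS, nothing is lost. If it adds something, a positive result is slightly understated, never overstated. All of this stands, and it limits the weight of the point. It does not remove it, since the better model costs nothing. The optional subgroup analyses are no substitute, because they do not adjust the primary estimate.

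A reader might go further in four ways that the article does not support.

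- **That omitting hospital also makes the standard error wrong.** Hospital is not a named stratum. For such a factor, chance imbalance between arms is part of the sampling variation that the standard error already measures.
- **That hospital imbalance biases the result.** Its expectation is zero, so it is random error. If the hospitals differed by 10 mm (an assumption without a source in the article) and patients split equally, its SD at 58 per arm would be √(2 × 0.25/58) × 10 = 0.93 mm. That is (0.93/4.59)², or about 4%, of the variance of the estimate.
- **That adding sex lifts power from 90% to 91%, 92% or 93%.** That takes the r² = 0 case as the starting point in every row and overstates the gain.
- **That the responder tests need the same repair.** They are secondary, and an unstratified chi-square test is at worst mildly conservative. Logistic regression would replace the planned comparison of percentages with a conditional odds ratio.

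**Conclusion.** The point holds as a free improvement to the primary analysis. Randomisation is stratified by sex alone, and the stated ANCOVA leaves sex out. For r² between 2% and 10%, an assumed range, the reported standard error is about 1% to 5% too large, the actual two-sided alpha is about 4.8% to 3.9%, and about 0.3 to 1.5 points of power are lost. At r² = 0 the loss is nil. The figures also rest on 58 completers per arm and on 24.71 as the residual SD.

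The omission does not bias the estimate, raise the false-positive rate or undermine the sample size: planned power stays above 90% throughout the range, and 73 per group stands. For hospital, the article supports only a suggestion about precision.

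**What to change.** In section 2.8, write the primary model as: change in VAS at 4 weeks = treatment + baseline VAS + sex. For the continuous secondary outcomes use treatment, the baseline value of that outcome and sex. Include sex in the multiple-imputation model, so that the imputation contains every term of the analysis model.

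Hospital may be prespecified as a further covariate, with precision in a two-hospital trial given as the reason; stratification is not the reason. The gain would be roughly 1 point of power if hospital explains about 5% of residual variance.

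The cost is one degree of freedom for sex and one more if hospital is added. No new data are needed and the sample size does not change. Fix the terms before unblinding, so that no choice between adjusted and unadjusted results remains afterwards. If an unseen analysis plan already includes sex, bring the article's wording into line with it.

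### The VAS responder outcomes are tested without adjusting for baseline VAS, which costs some power on the >15 mm responder (about 3 to 11 points under assumed correlations, fewer if entry criteria narrow the baseline range)

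*Protocol article*

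**What the plan says.** Section 2.6 (Outcome measures) makes clinical relevance a secondary outcome, assessed by "comparing the percentage of subjects who indicate an improvement of more than 15 mm on the VAS", with further cuts at >30% and >50%. It takes 15 mm as the minimal clinically important difference. Baseline VAS is available: "The baseline VAS score will be measured immediately before the first intervention".

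Section 2.8 (Statistical analysis) analyses the primary VAS change by "analysis of covariance with the covariates being the VAS score at baseline", with treatment group as the fixed factor, and extends this method to the secondary outcomes. It then makes an exception: "If the outcome variables are categorical data, they will be analyzed using the chi-square test or the Fisher exact test". No baseline-adjusted model is named for the responder outcomes. The article gives no power for them; section 2.3 sizes the trial on the mean VAS change only.

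**The concern.** The responder outcomes and the primary outcome come from the same two VAS readings. Baseline VAS usually predicts how far a subject can fall, partly through regression to the mean and partly because a low starter has little room to improve. The plan uses that information for the continuous change and discards it once the change is cut at a threshold.

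Two things follow. The comparison of >15 mm responders has less power than the collected data allow. Also, a chance baseline imbalance is corrected in the ANCOVA but passes into the responder percentages. Such an imbalance can occur because randomisation is stratified by sex and not by baseline VAS. At stake is the precision of the analysis that the plan uses to judge whether a VAS difference matters to patients.

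**Working it through.** **Inputs from the article (sections 2.3 and 2.8).** The mean difference "between the changes in the VAS before and after treatment in each group is 15"; "the standard deviation (σ) is 24.71"; "a significance level of 5%, a power of 90%, and an assignment ratio of the groups of 1:1"; two-sided testing ("All statistical analyses will be conducted using the 2-tailed test in principle"); 20% dropout.

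**Assumed inputs, not in the article.** Control-arm mean improvement of 5 to 20 mm; correlation of baseline VAS with improvement of 0.3 to 0.6; and, for the bounded model, the baseline mean and an entry floor. The entry criteria table is not shown in the text at hand.

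**1. The plan's own sample size.** n = 2(1.960 + 1.282)² × 24.71² / 15² = 57.03, so 58 per arm. Then 58 / 0.8 = 72.5, so 73 per arm and 146 in total. This reproduces the plan. Power for the mean difference at 58 per arm is 90.5%.

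**2. Unadjusted power for the >15 mm responder.** With normal improvements, the response proportion in an arm with mean improvement m is Φ((m − 15)/24.71).
- Control mean 15 mm: Φ(0) = 50.0%. Acupotomy mean 30 mm: Φ(15/24.71) = Φ(0.607) = 72.8%. Difference 0.228.
- Pooled proportion 0.614. SE under the null = √(2 × 0.614 × 0.386 / 58) = 0.0904. SE under the alternative = √((0.500 × 0.500 + 0.728 × 0.272) / 58) = 0.0879.
- Power = Φ((0.228 − 1.96 × 0.0904) / 0.0879) = Φ(0.58) = 71.9%.

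Over control means of 5 to 20 mm this formula gives 69-73%, and simulation gives 70-74%.

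**3. Which correlation is meant.** The gain depends on the correlation of baseline with improvement. If the baseline and 4-week SDs are equal and the two scores correlate at r, the correlation of baseline with improvement is √((1 − r)/2). So r = 0.5 gives 0.5, r = 0.3 gives 0.59, and r = 0.7 gives 0.39. A weaker correlation between the two scores therefore means a larger gain. All rows below use the correlation with improvement.

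**4. Adjusted power by simulation.** Uncorrected chi-square against logistic regression on treatment and baseline VAS (Wald to likelihood-ratio test), 58 per arm, normal unbounded changes, control mean 15 mm unless stated:

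| Correlation of baseline with improvement | Unadjusted | Adjusted | Gain (points) |
|---|---|---|---|
| 0.3 (control means 10-20 mm) | – | – | about 3-4 |
| 0.39 | 71.0% | 75.1-75.8% | 4.1-4.8 |
| 0.5 | 71.0% | 78.5-79.6% | 7.5-8.6 |
| 0.59 | 72.0% | 82.0-83.0% | 10-11 |
| 0.6 (control means 10-20 mm) | – | – | about 9-11 |

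At 0.5, over control means of 5 to 20 mm, the gain is 6.4 to 8.6 points. With all 73 per arm evaluable it is about 4 to 7 points. With no treatment effect, both tests reject in about 5% of trials.

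**5. Bounded VAS and an entry floor.** With the VAS held to 0-100, an assumed baseline mean of 65 mm, and floors of 30, 40 and 50 mm, the gains are about 4, 2-3 and 1-2 points. Bounded simulations with other assumed baseline settings gave about 3 to 6 points. Together: about 1 to 6 points.

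**6. The >30% and >50% responders.** The bounded model with a 30 mm floor gives −0.6 to +0.7 points. An unbounded model with assumed baseline mean 60 mm and SD 15 mm gives about 2-3. A percentage cut already scales with baseline, so little is left to recover.

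**The case against.** The strongest reply is that nothing here is an error. Chi-square or Fisher on raw proportions is a conventional, prespecified choice that holds the type I error. The outcome is secondary, and no power is claimed for it. Section 2.6 defines clinical relevance as the percentage of subjects who improve, and the planned test compares exactly that. The correlation, the control-arm improvement and the entry floor are all assumed, so any single figure for the gain would be too precise. All of this stands. It limits the point to an optional improvement, stated as a range and aimed mainly at one of the three cuts.

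A reader might infer more than the document supports:
- *That the test is biased or invalid.* It is not: randomisation protects the unadjusted comparison, and the simulated type I error is about 5%.
- *That lack of adjustment explains why responder power is well below 90%.* Most of the fall comes from cutting a continuous change in two: 90.5% − 71.9% = 18.6 points. At a correlation of 0.5, adjustment returns 7.5 to 8.6 of these, which is under half.
- *That adjustment would bring the responder result into line with the ANCOVA.* It removes one source of disagreement, baseline imbalance. The loss from dichotomising remains.
- *That subjects starting at or below 15 mm, who cannot respond, drive the loss.* That matters only if such subjects are enrolled, and the entry criteria are not visible here.

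What the reply does not remove is the gain on the >15 mm responder. The baseline score is already collected and already used as a covariate for the same VAS change. The choice of test is written into section 2.8, so it is not a detail merely left to a fuller plan.

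**Conclusion.** The point holds as a minor efficiency loss in a secondary outcome. For the >15 mm responder at 58 evaluable per arm, adjusting for baseline VAS would add about 3 to 11 points to a power of about 70-74% if the correlation of baseline with improvement lies between 0.3 and 0.6, and about 6-8 points at 0.5. With a bounded scale and an entry floor of 30-50 mm it would add about 1 to 6 points. For the >30% and >50% responders the gain is about 0 to 3 points and could be nil. Only the 15 mm difference, the SD of 24.71 and the sample size come from the article. The document does not support a loss of 6-8 points as a firm figure, or one of that size on all three cuts. The primary analysis and its conclusion are unaffected.

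**What to change.** In section 2.8, exempt the >15 mm VAS responder from the rule for categorical outcomes. Analyse it by logistic regression on treatment and baseline VAS (continuous), and report the baseline-standardised difference in response proportions with its 95% confidence interval. Report the raw percentages and the planned chi-square or Fisher test alongside as supporting results. The same model may be used for the >30% and >50% cuts, but little is gained there.

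The cost is one sentence in the plan and a few lines of SAS, with no new data or patients. The drawback is that a model-based estimate is slightly harder to explain than two raw percentages. Reporting a standardised risk difference, and not only an odds ratio, keeps the result on the scale that section 2.6 uses.
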